**Fig. 1 f0005:**
[figure not shown]
Study design flow-chart.

### Outcomes assessment

2.5

#### Primary outcome

2.5.1

The Primary outcome of the study is occurrence of falls. Falls will be measured at 3, 6, 12, and 24 months by research-assistant follow-up telephone calls for both the groups. A structured pre-tested questionnaire will be used to assess falls on telephonic interview. The interview will take 5–10 minutes of each participants to assess occurrence of any new fall incident after discharge. Falls will be assessed by comparing the number of falls in intervention and control groups.

#### Secondary outcome

2.5.2

Physical Mobility and Mobility-related disability will be measured with a self-reported test at every routine follow-up for up to two years using a performance-based test as per Haley et al. [26]. The performance-based mobility measure will be the lower extremity Summary Performance Score version of the Short Physical Performance Battery (SPPB) [27]. This battery gives a composite score based on timed performance of three mobility tasks: the ability to stand up for up to 10 seconds with feet in different positions (together side by side, semi-tandem and tandem), 4-meter walk and time to rise from a chair 5 times. The short performance based mobility tool is a valid and reliable tool with test retest validity ranging from 0.83 to 0.89. Study conducted by Gómez and colleagues in 2013 on adults between 65 to 74 years of age residing in the Andes Mountains of Colombia reported Test-retest reliability of 0.87 of the SPPB in Spanish version [28]. Another study conducted in Quebec and Brazil by Freire and colleagues in 2012 reported the validity and reliability of SPPB in diverse populations ranging from 0.83 to 0.89 [29]. This short performance battery tool had been validated in varied languages in different regions but not in Urdu language. Therefore, to use this tool in the study, we will perform back and forward translation of SPPB in Urdu language and will send it to 5–7 clinical experts to rate it for clearance and relevance in order to calculate the validity of tool in Urdu language.

### Follow-ups

2.6

For follow-ups, telephone calls and face to face interviews will be utilized. All the Patients (both groups) will be contacted after 3 months, 6 months, 12 months, and 24 months (Fig. 1) for the period of two years via telephone call to assess occurrence of fall. The call will take approximately 5–10 minutes of each patient. While, the performance-based mobility measure will be marked at every routine follow-up for up to two years using face to face interview to assess the overall trend. Furthermore, anthropometric assessment will also be done to assess weight loss at each follow-up.

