For many individuals, the risk of falls and disability after hospital discharge decreases with time. However, for a significant proportion, this is not the case [24]. Many patients after discharge are readmitted with second fracture to the hospitals due to lack of acute rehabilitation programs [25]. Therefore, we have designed a post-discharge home-based physical rehabilitation intervention program to minimize disability and falls in this high-risk elderly population. This study will evaluate the effectiveness of 12 week home-based physiotherapy program in reduction of secondary falls and improvement in physical mobility of elderly patients after hip fracture surgery.

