### Study design

2.1

This study will be an open label, simple randomized controlled trial at a single hospital. The two arms will be equally allocated on a 1:1 ratio into intervention and control groups. The control arm will receive the usual standard postoperative rehabilitation after a bipolar hemiarthroplasty/total hip arthroplasty which will include in hospital rehabilitation and a maximum of 5 physiotherapist visits postoperatively, arranged and funded by the patient as feasible. The intervention group will receive an extended home-based rehabilitation program twice a week continued for 3 months (12 weeks) after discharge funded by the study.

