### Statistical analysis

2.10

Intention to treat Analysis will be performed for both the groups. All the analysis will be done on STATA version 15.0 [32]. Baseline characteristics for both groups and changes from baseline to 6 months and baseline to 2 year will be compared in the two groups using the χ2 test, Mann-Whitney, or Student's t-test as applicable. The number of falls in both the groups will be compared by computing incidence ratio rates using negative binomial regression models after adjusting for baseline differences in fall rates along with incomplete/loss to follow‐up in a small percentage of subjects. Between group comparisons of final test performance for the continuously-scored outcome measures will be made using General Linear Models (ANCOVA) controlled for pre-test performance.

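### The SPPB is tied to undated routine visits, and the named change comparisons (6 months, 2 years) leave out the end of the 12-week programme

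*Protocol article*

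**What the plan says.** The Introduction states the aim as the "effectiveness of 12 week home-based physiotherapy program in reduction of secondary falls and improvement in physical mobility". Section 2.1 describes an "extended home-based rehabilitation program twice a week continued for 3 months (12 weeks) after discharge", so the programme ends at about month 3.

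Sections 2.5.1 and 2.6 set months 3, 6, 12 and 24 for telephone calls about falls in both arms. Section 2.6 then contrasts this with the mobility measure, which "will be marked at every routine follow-up for up to two years using face to face interview", the purpose being to see the overall trend. Section 2.5.2 says that mobility "will be measured with a self-reported test at every routine follow-up for up to two years using a performance-based test". Neither section gives a month for these visits.

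Section 2.10 states that "changes from baseline to 6 months and baseline to 2 year will be compared in the two groups". It adds an ANCOVA of final test performance for continuously scored outcomes, adjusted for pre-test performance, and does not say when the final test takes place. Section 2.2 gives 19 months of enrolment within a study lasting 24 months.

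**The concern.** Mobility is one of the two effects named in the aim, and the SPPB is its only described measure. The SPPB consists of timed stands, a 4-metre walk and chair rises, so it cannot be scored during the dated telephone calls. It depends on face-to-face visits for which the article gives no dates.

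Two things follow. First, if those visits fall at different times for different patients, scores from different stages of recovery after surgery are pooled, and the between-arm comparison becomes noisier or, if timing differs by arm, biased. Second, a reader who wants to know whether patients moved better when the programme ended finds no comparison named for that moment. A result at 6 months or 2 years answers a different question, namely whether any benefit lasted.

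**Working it through.** No figure in the plan states or decides this point. The check compares the sections and then does three short calculations.

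**1. Schedule of each measure against the programme**

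| Item | Where | Timing given |
|---|---|---|
| Programme | 2.1, 2.3 | 12 weeks (3 months) after discharge |
| Falls, by telephone | 2.5.1, 2.6 | 3, 6, 12, 24 months |
| SPPB, face to face | 2.5.2, 2.6 | every routine follow-up up to two years; no months |
| Change comparisons | 2.10 | 6 months, 2 years |
| ANCOVA | 2.10 | final test; time not stated |

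Month 3 is fixed for falls only. It is not attached to the SPPB in the text, and it is not a named change comparison. The overall trend mentioned in 2.6 has no matching analysis in 2.10.

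**2. Distance from the end of the programme** (months counted from discharge, an assumption)

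- 6 months is about 26 weeks: 26 − 12 = 14 weeks after the programme stops.
- 2 years is 24 months: 24 − 3 = 21 months after it stops.

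**3. Who can reach each time point**

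Inputs from 2.2: enrolment over 19 months, study length 24 months. Assumptions: uniform accrual, and all follow-up ends at month 24 of the study. A patient reaches follow-up month m only if enrolled by study month 24 − m, so the share is (24 − m)/19, limited to the range 0 to 1.

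- m = 3: 21/19, limited to 100%
- m = 6: 18/19 = 95%
- m = 12: 12/19 = 63%
- m = 24: 0/19 = 0%

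Month 3 is thus the only one of the four that every patient can reach. The named 2-year comparison can be reached by essentially nobody unless follow-up runs beyond the stated study period.

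**4. Illustration only: what fading would do to power**

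The protocol gives no power for mobility; section 2.7 covers falls only. Suppose a 3-month comparison had 80% power at a two-sided 5% level. The standardised effect (difference divided by its standard error) is then 1.96 + 0.84 = 2.80, and power is approximately Φ(effect − 1.96). Precision is taken as the same at both times.

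- Difference shrinks by 25%: 0.75 × 2.80 = 2.10; Φ(0.14) ≈ 0.56.
- Difference shrinks by 50%: 0.50 × 2.80 = 1.40; Φ(−0.56) ≈ 0.29.
- No shrinkage: power stays at 0.80.

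Both the starting power and the shrinkage are assumed. The lines show how sensitive a 6-month comparison is to fading, not that fading will occur.

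**The case against.** The strongest counter-argument is that this is a condensed article. Visit windows and the main time point of a secondary outcome commonly stand in the full protocol or analysis plan, and Fig. 1, which is cited for the follow-up schedule, is not shown. That is fair for missing windows taken alone. It does not cover what the article itself does: it dates one outcome, places the other on a separate and undated footing, and names comparison times that pass over the end of the programme.

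Three stronger readings are tempting, and the documents do not support them.

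- *The effect at programme end is never tested.* This does not follow. The final test in the ANCOVA has no stated time, so an end-of-programme test is not excluded, although with testing for up to two years the last visit is the plainer reading. Nor does the sentence naming 6 months and 2 years mention the SPPB by name.
- *The SPPB visits are unscheduled and driven by clinical course, so the frailest drop out.* The text says routine, not unscheduled. Those visits may coincide with months 3, 6, 12 and 24. Nothing is said about attendance by arm or frailty, and drop-out would also affect fixed visits.
- *The control arm catches up, so a real benefit would be missed at 6 months.* The Introduction does say that, for many, "the risk of falls and disability after hospital discharge decreases with time". It adds at once that for a significant proportion this does not hold. It gives no SPPB course by arm.

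It is also true that the aim does not require mobility to be judged at week 12. A lasting effect of a 12-week programme is a legitimate target, and the choice of main time point belongs to the sponsor.

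**Conclusion.** The point holds in a limited form. The SPPB has no stated assessment months, while the falls calls do. The only named change comparisons come about 14 weeks and 21 months after the programme ends, the end of the programme is not among them, and the final test in the ANCOVA is undefined. Scores may therefore come from different stages of recovery, and the immediate effect on half of the stated aim has no named comparison.

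The calendar adds weight. Under uniform accrual and a study that stops at 24 months, the plan names a time point that essentially no patient reaches and leaves unnamed the one that all can reach.

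How much power or bias is at stake cannot be read from the documents. The figures of about 56% and 29% hold only under the assumed shrinkage. This concerns a secondary outcome and leaves the falls comparison untouched. It is a worthwhile, inexpensive improvement rather than a flaw that invalidates the trial.

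A separate wording error sits in the same section: 2.5.2 calls the measure self-reported and performance-based in one sentence, whereas the SPPB it describes is performance-based only.

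**What to change.** - **Sections 2.5.2 and 2.6:** schedule the face-to-face SPPB at the same fixed months as the falls calls, including month 3, with the same windows in both arms.
- **Section 2.10:** add a 3-month baseline-adjusted (ANCOVA) comparison alongside the later ones, and state which visit is the final test. Which time point is the main one is for the sponsor to choose and state.
- **Sections 2.2 and 2.10:** reconcile the 2-year comparison with 19 months of enrolment in a 24-month study, since the two cannot both stand as written. The same reconciliation decides whether a 24-month SPPB visit is feasible.
- **Section 2.5.2:** remove the description of the SPPB as self-reported.

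The cost is mainly wording and visit booking. Some patients will need a visit arranged near month 3. If routine visits do not already match the other fixed months, more bookings follow. There is also one more secondary comparison to report.

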### Sample size

2.7

Open Epi was [30] used to compute sample size for the study. The retrospective analyses of studies have showed that reported incidence of falls in elderly patients is between 30–40% globally [31]. Therefore, 40 % fall rates were considered for control group to calculate sample size. Moreover, based on evidences from previous studies, home-based rehabilitation program can reduce incidence of falls up to 20% [11]. Henceforth, considering 40% fall rates in control group with an absolute risk reduction of 20% in intervention group, power of 0.8 and two sided confidence interval of 95% yields a sample size of 94 per group. Adding 20% attrition rate, the final sample size is calculated to be 112 per group.

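### The 94 per group in section 2.7 cannot be reproduced from its stated inputs, which give 82, 83 or 91; the discrepancy is conservative and needs only a corrected sentence

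*Protocol article*

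**What the plan says.** Section 2.7 (Sample size) of the protocol article gives all the inputs of a two-proportion calculation. For the control group, "40 % fall rates were considered for control group to calculate sample size". The effect is set by "considering 40% fall rates in control group with an absolute risk reduction of 20% in intervention group", which makes the intervention proportion 20%. The result follows in the same sentence: "power of 0.8 and two sided confidence interval of 95% yields a sample size of 94 per group". Section 2.1 (Study design) gives the allocation: "The two arms will be equally allocated on a 1:1 ratio into intervention and control groups". On the tool, section 2.7 says only "Open Epi was [30] used to compute sample size for the study". It names neither the formula nor whether a continuity correction was applied. The 94 is then raised for 20% attrition to 112 per group, which is the 224 of section 2.2 (Recruitment).

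**The concern.** Inputs and result are printed as one calculation, so a reader should be able to repeat it, and the usual formulas give smaller numbers. The 94 is the base of the recruitment target, and 80% is the only power that the article states. If the two do not match, the article leaves unclear what power the design has for a fall from 40% to 20%. An error in the other direction would have meant a trial too small for its own target, so the direction and size of the gap need to be established.

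**Working it through.** **Inputs.** p1 = 0.40 and p2 = 0.40 − 0.20 = 0.20 (section 2.7); mean proportion 0.30; difference d = 0.20; two-sided 5% level, z = 1.960; power 0.80, z = 0.842 (section 2.7); 1:1 allocation (section 2.1). Two sums recur: 2 × 0.30 × 0.70 = 0.42, and 0.40 × 0.60 + 0.20 × 0.80 = 0.40.

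**Attempt to reproduce 94 per group.**

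- Fleiss, no correction: (1.960 × √0.42 + 0.842 × √0.40)² / 0.04 = (1.270 + 0.532)² / 0.04 = 81.2, so 82.
- Kelsey: (1.960 + 0.842)² × 0.42 / 0.04 = 7.849 × 10.5 = 82.4, so 83.
- Unpooled variance: 7.849 × 0.40 / 0.04 = 78.5, so 79.
- Arcsine: 80.3, so 81.
- Fleiss with continuity correction, starting from n = 81.2: (n/4) × (1 + √(1 + 4/(n × d)))² = 20.3 × (1 + 1.116)² = 90.9, so 91.
- Smallest size with 80% power by Fisher's exact test: 90.

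None gives 94. The nearest usual result is 91, which is 3 lower. Applying the continuity correction to the Kelsey figure gives 92.1, so 93; that is not a usual pairing and still misses.

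**Other readings of the text.** A one-sided test gives 64, or 74 with correction. Taking the 20% as a relative reduction (40% v 32%) gives 564. Neither explains 94.

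**Power at 94 per group for 40% v 20%.**

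- Uncorrected, normal approximation: (0.20 − 1.960 × √(0.42/94)) / √(0.40/94) = (0.20 − 0.1310) / 0.0652 = 1.058, so 85.5%.
- Uncorrected chi-square, full binomial enumeration: 85.7%.
- Continuity-corrected, normal approximation (0.20 reduced by 1/94): 0.894, so 81.4%.
- Continuity-corrected chi-square, full binomial enumeration: 81.9%. Fisher's exact test: 81.9%.

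**After the planned attrition.** 112 × 0.8 = 89.6 per group. Exact power at 89 and 90 per group is 83.7% and 84.2% uncorrected, and 79.6% and 80.2% continuity-corrected. The 224 enrolled therefore still carry about 80% power or more on the stated inputs.

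**The case against.** The best defence is that the gap is small and harmless. Section 2.7 does not name its formula, so a continuity-corrected or exact calculation cannot be excluded. Under either, 94 per group has about 82% power, within 2 points of the printed 80%, and exceeds the required size by only 3 or 4. Every two-sided size found for 80% power, from 79 to 91, lies below 94. All of this stands, and it keeps the point minor. It does not rescue the sentence, because section 2.7 says that the inputs yield 94, not that 94 gives at least 80% power.

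A reader might infer more than the article supports:

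- *That the printed size and power are incompatible.* This holds only for an uncorrected test, where the gap is 85.7 − 80 = 5.7 points.
- *That section 2.10 (Statistical analysis) fixes an uncorrected chi-square test for falls.* It does not. The comparisons that "will be compared in the two groups using the χ2 test, Mann-Whitney, or Student's t-test as applicable" are those of baseline characteristics and of changes from baseline. No form of the chi-square test is specified, and the number of falls is compared by negative binomial regression.
- *That other inputs were entered in the software.* 50% v 30% at 80% power, or 40% v 20% at 85% power, gives about 93 to 94 by the uncorrected formulas. But the text states 40% and 0.8 explicitly, and inputs found by searching for a match are not evidence that they were used.
- *That the detectable effect is misreported.* The target of 40% v 20% is stated plainly, and 94 per group has at least 80% power for it.

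**Conclusion.** The point holds as a minor reporting error. From 40% v 20%, 80% power, a two-sided 5% level and 1:1 allocation, the base size is 82 or 83 per group without continuity correction and 91 with it, not 94. The excess is 11 to 12, or 3, per group. At 94 the power is about 86% or 82% instead of 80%. On its own inputs the trial is not underpowered by this error. The conclusion assumes that the calculation compares two independent proportions, as the inputs imply, and that the 20% is an absolute reduction, as section 2.7 says. The article does not show how 94 arose.

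**What to change.** Rerun the calculation and rewrite the sentence in section 2.7 so that formula, inputs, size and power agree. There are two ways to do so:

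- Keep 80% power and print 82 (Fleiss) or 83 (Kelsey) without continuity correction, or 91 (Fleiss) with it.
- Keep 94 and restate the power for 40% v 20% as about 86% (uncorrected chi-square) or about 82% (continuity-corrected), naming which.

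Then carry the chosen base size into the attrition step in the same section and show that step, so that the path to 112 per group can be followed. The cost is one corrected sentence. No extra patients, staff or procedures are needed, and the 224 to be enrolled can stay.

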### Recruitment

2.2

The study will be conducted solely at Aga Khan University Hospital. The care providers involved with the study will include Orthopaedic consultants, Family medicine physician, physiotherapist, and Orthopaedic nurses. We will recruit 224 elderly patients aged 60 years and above undergoing hip fracture surgery who will be randomly divided into intervention and control arms. Participants will be enrolled by research-assistant over a 19‐month period from Emergency Room and Orthopedic outpatient clinics. This study will be conducted over a period of 24 months with ongoing recruitment and follow-ups after intervention.

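### The 20% attrition allowance multiplies by 1.2 instead of dividing by 0.8, so 112 per group leaves 89 to 90 after 20% loss, not 94; the effect on power is small

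*Protocol article*

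**What the plan says.** The sample size paragraph (Section 2.7) works from a comparison of two proportions in OpenEpi. For the control arm, "40 % fall rates were considered for control group to calculate sample size". The target effect is "an absolute risk reduction of 20% in intervention group", that is 40% against 20%. The error rates are given as "power of 0.8 and two sided confidence interval of 95" per cent. From these the calculation "yields a sample size of 94 per group". The last step is the attrition allowance: "Adding 20% attrition rate, the final sample size is calculated to be 112 per group".

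Allocation is equal (Section 2.1: "The two arms will be equally allocated on a 1:1 ratio"), and Section 2.2 carries the result forward as 2 × 112: "We will recruit 224 elderly patients". No other attrition figure or inflation formula appears in the article.

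**The concern.** The starting figure, the attrition rate and the final figure stand in one paragraph and do not fit together. An attrition rate is a fraction of the patients enrolled. If 20% of 112 are lost, the group left is smaller than the 94 that the same paragraph derives as the requirement.

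At stake is the use made of the statement. Anyone watching retention against Section 2.7 would take 20% loss as covered, although on a base of 94 the margin is used up at about 16%. Follow-up runs to 24 months in patients aged 60 and over after hip fracture surgery, so the allowance may well be needed. A reader also cannot recover the 94 from the stated inputs, because the software is named but the formula is not.

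**Working it through.** **Inputs, all from Section 2.7 except the allocation (Section 2.1):** p1 = 0.40, p2 = 0.20, difference 0.20, mean proportion 0.30; two-sided 5% level (z = 1.96); power 0.80 (z = 0.8416); 1:1 allocation; stated base 94 per group; attrition 20%; stated final size 112 per group.

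**Step 1: where 112 comes from.**
- Multiplying: 94 × 1.2 = 112.8. Rounded down this is the stated 112; rounded up it would be 113.
- Dividing by the fraction retained: 94/(1 − 0.20) = 117.5, so 118 per group and 236 in total. This does not give 112.

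The plan's figure is therefore the multiplicative form, rounded down.

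**Step 2: what 112 delivers.**
- Remaining after 20% loss: 112 × 0.80 = 89.6, so 89 or 90 per group, 4 to 5 short of 94.
- Loss that still leaves 94: 1 − 94/112 = 16.1%.

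**Step 3: two-proportion power for 40% against 20%.**

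Uncorrected: Φ{[0.20 − 1.96 × √(2 × 0.3 × 0.7/n)] / √((0.24 + 0.16)/n)}. The continuity-corrected version also subtracts 1/n from the 0.20.

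| n per group | uncorrected | continuity-corrected |
|---|---|---|
| 89 | 83.5% | 79.0% |
| 90 | 83.9% | 79.5% |
| 94 | 85.5% | 81.4% |

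The slip costs about 2 percentage points of power on either version.

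**Step 4: does 94 follow from the inputs?**
- Fleiss: n = [1.96 × √(2 × 0.3 × 0.7) + 0.8416 × √(0.24 + 0.16)]² / 0.04 = 81.2, so 82.
- Kelsey: n = (1.96 + 0.8416)² × 2 × 0.3 × 0.7 / 0.04 = 82.4, so 83.
- Fleiss with continuity correction: (81.2/4) × [1 + √(1 + 4/(81.2 × 0.20))]² = 90.9, so 91.

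None gives 94. The stated base is 3 above the nearest of them, on the conservative side.

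**Step 5: what 112 tolerates for each candidate base.**

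| base n | enrolled needed for 20% loss | loss that 112 tolerates |
|---|---|---|
| 94 | 117.5, so 118 | 16.1% |
| 91 | 113.75, so 114 | 18.75% |
| 83 | 103.75, so 104 | 25.9% |
| 82 | 102.5, so 103 | 26.8% |

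**The case against.** The strongest reply is that the shortfall exists only against a base that the stated inputs do not need. If the base were 82 or 83, 112 per group would cover 20% attrition with room to spare; if it were 91, it would be 2 per group short. This stands as a limit on the consequence, and it means that the tolerated attrition cannot be restated until the base is settled. It does not rescue the paragraph, which gives 94 as its base and an allowance that does not preserve it.

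A second reply is that the article never says in words that 94 will remain evaluable, so the 20% could be a simple mark-up. But the text calls it an attrition rate, and an allowance for attrition has no other purpose than to protect the required number.

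A third reply concerns the analysis. Section 2.10 plans an intention-to-treat comparison of fall counts by negative binomial regression, with adjustment for incomplete follow-up, and falls are asked about at 3, 6, 12 and 24 months. A patient lost after month 6 or 12 has already supplied data. Counting every lost patient as contributing nothing is a worst case, and the power figures above are not the power of that model. This stands, and the figures must be labelled accordingly.

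Finally, the OpenEpi settings are not shown and the article is condensed, so 94 may have a source that is not visible. The claim here is only that the three formulas above do not give it.

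**Conclusion.** The attrition step is wrong as written. On the plan's own base of 94, 112 per group leaves 89 to 90 after 20% loss and tolerates only about 16%. The figure that would keep both 94 and 20% is 118 per group.

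A reader might infer that the trial is seriously underpowered, or that recruitment must rise to 236. The documents do not support either. At 89 to 90 per group, power for 40% against 20% is about 84% uncorrected, above the 80% planned, and 79.0% to 79.5% with continuity correction, at most 1 point below it. Nor is the unexplained 94 a further weakness in size: it lies above what the stated inputs require and partly offsets the attrition slip.

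The arithmetic in Steps 1 and 2 needs only the figures in Section 2.7. The power figures assume a two-proportion comparison, a true 40% against 20%, and no data from lost patients. They say nothing exact about the planned negative binomial analysis.

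**What to change.** Rewrite the end of Section 2.7, leaving the 112 per group and the 224 in Section 2.2 unchanged:

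- Name the OpenEpi formula used and settle one base figure that it gives, or explain the 94.
- For that one base, state the attrition that 112 per group tolerates: about 16% if 94 is kept, about 19% if it is 91, about 26 to 27% if it is 82 or 83.
- State that 20% loss leaves 89 to 90 per group, with about 84% power uncorrected or 79% with continuity correction for 40% against 20%, labelled as two-proportion power assuming that lost patients contribute no data.

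The cost is one paragraph of wording, with no added participants and no change to the design or analysis. The one downside is that, if the base is 94 or 91, the stated attrition tolerance becomes slightly less favourable than 20%.
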